## Abstract

**Background:**

Oral anticoagulant drugs represent an essential tool in the prevention of thromboembolic events. The ones in widespread use are vitamin K antagonists, whose plasma level is monitored by measuring prothrombin time using the international normalized ratio. If its values are out of the recommended range, the patient will have a higher risk of suffering from thromboembolic or hemorrhagic complications. Previous research has shown that approximately 33% of patients keep having values at an inappropriate level. The purpose of the proposed study is to improve the international normalized ratio control results by a joint didactic intervention based on the Junta de Andalucía School for Patients method that will be implemented by anticoagulated patients themselves.

**Methods:**

A randomized controlled trial will be undertaken at primary care centers from one healthcare area in Málaga (Andalusia, Spain). Study population: patients participating in an oral anticoagulant therapy program of vitamin K antagonists.

First step: identification of patients in the oral anticoagulation therapy program with international normalized ratio control of the therapeutic level at 65% or less over total time. Second step: patients with international normalized ratio (INR) control figures under 2 or above 3 will be assigned to two different groups:

Group 1 or joint intervention group: patients will be instructed in the joint didactic “from peer to peer,” by a previously trained and expert anticoagulant patient.

Group 2 or control group: the control group will receive the usual clinical practice. They will be evaluated by nurses about once a month, except for cases in which their INR figures are under 2 or above 3, and those patients will be evaluated more frequently.

A total of 312 individuals will be required (156 in each group) to detect differences in INR figures equal to or higher than 15% between the groups.

Study variables: time on therapeutic levels before and after the intervention; sociodemographic variables; vital signs; the existence of cardiovascular risk factors or accompanying diseases in the clinical records; laboratory test including complete blood counts, bleeding time, and prothrombin time or partial thromboplastin time; and blood chemistry, other prescribed drugs, and social support.

A quasi-experimental analytic study with before-after statistical analysis of the intervention will be conducted. Linear regression models will be applied for the main variable results (international normalized ratio value, time on therapeutic level) inputting sociodemographic variables, accompanying diseases, and social support.

**Trial registration:**

ClinicalTrials.gov NCT03647254. Registered on 27 August 2018

## Background and current status

It has been proven that oral anticoagulant therapy (AOT) is effective in preventing situations with a high risk of thromboembolic events and in treating them [1, 2]. It significantly decreases ischemic stroke rates as well as their severity and associated death risk.

However, it is a therapy with special features, such as doses and response variability, a narrow therapeutic range, interactions with other drugs and foods, and potentially severe side effects. These facts compel the investigators to undertake close monitoring of these patients [2].

An important effect in developing cardioembolic or hemorrhagic events due to inappropriate coagulation control values using vitamin K antagonists (VKA) has been found, because control variations around 15% could result in relevant clinical problems [1].

The main AOT indications are deep vein thrombosis, pulmonary embolism, and embolic condition prevention in patients suffering from atrial fibrillation or heart prosthetic valve wearers [3, 4]. Atrial fibrillation (AF) is currently the pathology that has the most anticoagulant therapy indications. This fact is partially due to the aging of the population, since there are both incidence and prevalence increases of this arrhythmia, among older patients [5, 6]. Control of patients on AOT was performed in hospitals until a few years ago. Nevertheless, changes in social and health contexts besides the expansion of the use of these drugs have placed them in the purview of primary health care. The development of handheld coagulation measuring devices and the need to improve patients’ accessibility had been used to justify the decentralization of control. Currently, AOT monitoring is carried out on stable patients in primary care [7, 8].

When a need for receiving anticoagulation has been established, this could be implemented by using heparin or vitamin K antagonists (acenocoumarol or coumadin) or newer direct action oral anticoagulants such as dabigatran, rivaroxaban, apixaban, or edoxaban [9, 10].

A method of standardizing prothrombin time results, called the international normalized ratio (INR) system, allows for reliable results to be obtained from different laboratories [11].

The development of coagulation handheld measuring devices to match INR in the capillary blood with a high sensitivity and reliability has made anticoagulant therapy controls in primary care possible. Their use allows for a comprehensive approach and control of these patients.

The number of patients with AF on anticoagulation with VKA is high; however, the INR level control results are not ideal [12–14].

Through educational and behavioral interventions, VKA-anticoagulated patients can increase their knowledge and understanding of the action mechanisms of anticoagulant drugs. As a consequence, patients may increase their ability to maintain INR appropriate control. A recent study regarding these interventions noted that education is particularly important to provide information about safety for patients suffering AF on AOT. In addition, education allows them to make their own well-founded decisions about treatment options and to manage their AOT. However, there are not enough evidences to establish definite conclusions about these interventions [15]. However, three research articles recently conducted in Spain show high out of range anticoagulation control levels in patients on VKA [16–18].

However, there is not enough evidence to establish definitive conclusions about educational health interventions on the INR behavior of patients suffering from AF on OAT [19, 20].

Furthermore, it should be noted that these chronic patients are prone to suffer from many other conditions and, as a result, they are likely to take many medications. This factor makes health self-management less effective. Hence, educative aspects aimed at self-care and effective health self-management are necessary components of educational interventions targeting this type of patients [21, 22]. Self-care support programs are presented as a tool to accomplish a change. This tool or method is also presented as an alternative to the paternalistic method in which citizens could receive more information (this fact is in accordance with a demonstrated increase in people’s request for health issues via the Internet).

### Aim

The present study aims to show that conducting an organized group educational intervention on VKA-anticoagulated patients by using the Junta de Andalucía School for Patients method will result in reductions in inappropriate INR control levels.

## Methods

The investigators will perform a randomized single-blind trial over a period of 28 months. The study started on 1 September 2018 and will end on 31 December 2020.

### Study area

One healthcare area in Málaga (Spain) where 741,000 inhabitants from rural or urban population are cared for. It is organized into 33 primary care centers and 19 local doctors’ offices.

### Study population

Participants are affiliated to four different primary care centers representing people from different social classes in Málaga city.

### Inclusion and exclusion criteria

#### Inclusion criteria

Men and women over 18 years old affiliated to one of the 4 primary care centers selectedPatients on VKA treatment for at least the last 6 months in a primary care environmentPatients showing INR level control values under 2 or above 3 (out of range)Patients for whom we have access to, at least, 80% of their INR level controls in the last 6 months of treatment with VKA, even though they are enrolled in another primary care centerPatients who give written informed consent to take part in the study

#### Exclusion criteria

Patients suffering from cognitive impairment that prevents them from understanding what is written in the information sheet and consent formLimited mobility patientsTerminal patientsAlcoholism or drug addictionSevere psychiatric illnessAny other reason that prevents them to be present at center’s meetings

### Setting the limits and justification of the sample size

The total population from the health centers participating in the study amounted to approximately 50,000 inhabitants.

#### Step I

Considering that the prevalence of patients on AOT is about 1.5% of the general population, it can be claimed that the target population to initiate our study will be 750 anticoagulated patients (using anticoagulant drug consumption data from our health área in Málaga, Spain). Prior studies indicated [15–17] that at least 33% of these patients would not have an appropriate INR control level (INR values above 2 and under 3 or under 3.5 for prosthetic valve wearers). To reach an appropriate sample size in the estimated proportion, the following terms must be considered: (1) using a normal asymptotic confidence interval with a correction to finite populations on bilaterally of 95%, (2) assuming that the expected population is approximately 33%, and (3) since the population total size is 750, it was deemed necessary to include 312 experimental units in this study (Fig. 1).

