#### Step II

Accepting an alfa risk of 0.05 and a beta risk of 0.20 in a bilateral comparison between the study group and the control group, 312 individuals will be required (156 in each group) to detect differences in INR figures equal or higher than 15% between the groups for the primary target. It has been estimated by the researches that there will be a tracking loss rate of 10%. It will be assumed these lost individuals are impossible to locate or are those who do not wish to take part or cannot attend the scheduled revisions, in accordance with the study intervention plan, as well as deaths occurring within 6 months of the intervention. Given the relevant impact of the development of cardioembolic or hemorrhagic events due to out of range INR control values, changes of approximately 15% could have significant clinical relevance.

Patients will be recruited from the list of patients taking anticoagulant drugs included in the digital medical record according to the inclusion and exclusion criteria. The recruitment period will last for 1 month.

To reach the required sample size, all patients from the four health centers on AOT using vitamin K antagonists will be studied. Patients will be selected from their own PCC once identified by “Seguridad Social de Andalucia” user number (NUSSA). Once the inappropriate individuals are identified, they will be consecutively placed considering their social security number in every health center. After that, patients in each strate (PCC) will be randomly distributed in the intervention group or the control group. The investigators will try to avoid bias depending on each health center issues.

It has been estimated a follow-up loss ratio of approximately 10%. Deaths 6 months from the intervention, and inability to locate individuals, or not attending to the scheduled meetings will be considered as losses when dealing with the study intervention program.

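### At the plan's 33% planning value the four centres hold about 248 poorly controlled patients, not the 312 to be randomised, and the basis for 312 is not given

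*Protocol article*

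**What the plan says.** The sample-size section builds up the source population in stages. It begins: "The total population from the health centers participating in the study amounted to approximately 50,000 inhabitants". Step I then takes the "prevalence of patients on AOT is about 1.5% of the general population" and concludes that "the target population to initiate our study will be 750 anticoagulated patients". On poor control it says that "at least 33% of these patients would not have an appropriate INR control level", and its calculation works from the same value ("assuming that the expected population is approximately 33" per cent). Step I ends with 312 experimental units, from a confidence interval for a proportion with a finite-population correction.

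Step II gives the same number for a different purpose: "312 individuals will be required (156 in each group) to detect differences in INR figures equal or higher than 15% between the groups", at a two-sided alpha of 0.05 and a beta of 0.20, with a 10% loss expected. The abstract repeats 312 and 156 per group. On where the patients come from, Step II says: "To reach the required sample size, all patients from the four health centers on AOT using vitamin K antagonists will be studied".

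The sections Second step and Timetable and work program confine the list for randomisation to patients with inappropriate INR control.

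**The concern.** Step I needs a sample from all anticoagulated patients. Step II needs patients from the poorly controlled subset. The article uses 312 for both and never compares the Step II number with the expected size of the subset. On its own figures the subset is smaller than 312, and the plan names no further source because the four centres are already taken in full.

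At stake is the only stated size and power for the primary comparison. If the number required is not expected to be available, the stated 20% beta risk has no basis as written. The intervention is sized to match: eleven sessions of up to 15 people hold 165, which fits an arm of 156.

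**Working it through.** **Source population.** 50,000 × 0.015 = 750. This reproduces the article's figure.

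**Step I's 312.** The usual formula is n = N·z²·p(1−p) / [d²(N−1) + z²·p(1−p)], with N = 750, p = 0.33 and z = 1.96. The half-width d is not stated. Assuming d = 0.04:
- z²·p(1−p) = 3.8415 × 0.2211 = 0.849
- n = 750 × 0.849 / (0.0016 × 749 + 0.849) = 311.1, rounded up to 312

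A half-width of 3 points gives 418 and one of 5 points gives 234. So 312 fits a prevalence sample drawn from all 750. That origin is an inference; the shortfall does not depend on it.

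**Step II's 312.** No control rate, SD or scale is given, so 312 cannot be derived from the stated inputs. Some assumed pairs of proportions come close: 60% v 75% needs 152 per arm, and 65% v 80% needs 138, or 154 after allowing for 10% loss. On a mean scale, 156 per arm for 15 points implies an SD of about 47 points.

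**Expected pool.**
- 750 × 0.33 = 247.5, about 248 (124 per arm)
- 312 − 248 = 64 short; 248/312 = 79%
- Share of all 750 needed for 312: 312/750 = 41.6%
- Share needed if 312 must remain after 10% loss: (312/0.9)/750 = 46.2%

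The 248 is an upper figure at the 33% planning value. The 750 counts all oral anticoagulation, whereas inclusion requires at least 6 months on a VKA, access to 80% of INR records, and consent. Six exclusion criteria also apply.

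**Power under three readings** (two-sided 0.05; 223 is 248 less 10%).

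1. *312 analysed is what 80% power requires.* The implied standardised effect is 2.80 × √(2/156) = 0.317. With 124 per arm, 0.317 × √(124/2) − 1.96 = 0.54, so power is about 70%. With 223 analysed it is about 66%. If 312 already allows for the 10% loss (about 281 analysed), 223 analysed gives about 70%.
2. *15 points between proportions.* With 124 per arm, power is 78% (33% v 18%), 67% (33% v 48%) or 66% (42.5% v 57.5%). The full 156 per arm gives 86%, 77% and 76% for the same pairs.
3. *15 points of mean time in range, assumed SD 20–30.* With 124 per arm, power is 97.6% at SD 30 and higher at smaller SDs. With about 111 per arm it is still 96% or more.

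**The case against.** Two stronger readings are tempting, and the other side answers both.

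A reader might infer that 312 cannot be recruited. The article gives 33% as a floor, from earlier studies not shown here, and does not say that they used this trial's cut-offs (time in range under 65%, or under 60% of measurements). A share of 41.6% or more is not shown to be impossible. This stands: the documents support only that 312 is not reached at the planning value.

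A reader might also infer that the trial is underpowered. The primary variable is described as quantitative and the groups are compared by t test or Mann-Whitney test. On that scale, 15 points would be detected with high power even after the shortfall. The proportion reading does not isolate the shortfall either, because two of its three scenarios miss 80% even at 156 per arm. This also stands: without a scale, SD or control rate, true power cannot be fixed.

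The 223 is not firm. Step II counts people unwilling to take part within the 10% loss, no exclusions have been deducted, and under intention-to-treat with record-based INR data non-attenders need not leave the analysis.

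Finally, the list of poorly controlled patients is completed before randomisation, so a shortfall would be known before allocation. That limits the harm. It does not reconcile the two numbers, since the article attaches no restatement of size or power to that step.

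**Conclusion.** The inconsistency is real and needs correcting. At the planning value the pool is at most about 248, which is 64 (21%) below the 312 stated in the abstract and Step II, with no reserve beyond the four centres. This rests only on the article's 50,000, 1.5% and 33%, and on randomisation being confined to poorly controlled patients.

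The effect on power is conditional. Either 312 is truly required, and about 248 delivers roughly 70% (about 66% with 223 analysed) instead of 80%; or the 15% is a mean difference in time in range with an SD near 20–30 (assumption), and 248 is ample while 312 lacks a justification. On both readings the stated size and its rationale do not fit together. The article supports neither a claim that 312 is unattainable nor an unconditional claim of low power.

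**What to change.** - In the abstract and Step II, replace 312 (156 per group) with the attainable number: all eligible, consenting, poorly controlled patients in the four centres, at most about 248 at the 33% planning value.
- State what the 15% is (points of mean time in range, or a difference in proportions) and the SD or control rate behind it.
- Restate the power, or the detectable difference in time in range, for the attainable number, and say whether that number is before or after the 10% loss.
- Update the figure from the Step I census before randomisation, when no outcome data exist.

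This changes protocol wording only. The cost is a less favourable stated size; no extra patients or centres are needed. Should the restated assumptions show that 312 is indeed required, the source population would have to be about 312/0.33 = 945 anticoagulated patients (about 63,000 inhabitants at 1.5%), before exclusions and refusals.

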**Fig. 1 Fig1:**
[figure not shown]
Study flow chart

#### Step II

Accepting an alfa risk of 0.05 and a beta risk of 0.20 in a bilateral comparison between the study group and the control group, 312 individuals will be required (156 in each group) to detect differences in INR figures equal or higher than 15% between the groups for the primary target. It has been estimated by the researches that there will be a tracking loss rate of 10%. It will be assumed these lost individuals are impossible to locate or are those who do not wish to take part or cannot attend the scheduled revisions, in accordance with the study intervention plan, as well as deaths occurring within 6 months of the intervention. Given the relevant impact of the development of cardioembolic or hemorrhagic events due to out of range INR control values, changes of approximately 15% could have significant clinical relevance.

Patients will be recruited from the list of patients taking anticoagulant drugs included in the digital medical record according to the inclusion and exclusion criteria. The recruitment period will last for 1 month.

To reach the required sample size, all patients from the four health centers on AOT using vitamin K antagonists will be studied. Patients will be selected from their own PCC once identified by “Seguridad Social de Andalucia” user number (NUSSA). Once the inappropriate individuals are identified, they will be consecutively placed considering their social security number in every health center. After that, patients in each strate (PCC) will be randomly distributed in the intervention group or the control group. The investigators will try to avoid bias depending on each health center issues.

It has been estimated a follow-up loss ratio of approximately 10%. Deaths 6 months from the intervention, and inability to locate individuals, or not attending to the scheduled meetings will be considered as losses when dealing with the study intervention program.

#### Study design

Randomized single-blind controlled trial.

### Description of the intervention

The study will be carried out over a 28-month period. It started on 1 September 2018, and it will finish on 31 December 2020. Participants will be contacted by phone. Trial information with details will be explained to them, and they will be asked whether they are interested in taking part. At the same time, they will be scheduled for the group meetings. Signed informed consent forms will be obtained when the patient attends the health center before the group meetings begin. Patients in each strate (PCC) will be randomly distributed to the intervention group or the control group (a random numbers table will be used). The allocation sequence will be generated by the researcher team. The allocation concealment mechanism consists of organizing patients considering their Andalusian Health Service Number of Clinical Record (AHNCR). After assignment to an intervention, participant names will be deleted by the nurses in charge of the recruitment in order to mask the data. The outcome assessors will not know the patients’ identity. The masking will be carried out by replacing the patients’ identification data with an assignment number.

All patients under study will receive an information sheet, and they will sign informed consent forms when they attend to INR control appointments. The investigators will try to encourage the involvement of every person so that patients included in the intervention group will be telephoned in previous weeks in order to achieve attendance at group meetings (at least three times and at different times if necessary) by a nurse. They will be recalled the day before the meeting as a reminder. After that, the intervention will be carried out and it will be based on the patients’ attendance of an educational session led by an expert patient (a member of the “Málaga anticoagulated patients association”). This person had been previously trained by health professionals and is able to take on a leadership role as an instructor, providing support through their knowledge and experience. Written material and a questionnaire form were developed for the intervention group before the meeting (Anexo VII). The patients are asked to answer questions about their vitamin K antagonist knowledge. Then, the expert patient will answer this question for everyone “what obstacles could we find when trying to reach an appropriate anticoagulation?” The instructor will rely on the support of short PowerPoint presentations as well as on graphic material explaining the subjects to the patients. The main explanations for inappropriate control values will be provided by the expert patient: other drug consumption, inadequate food, adherence to treatment, etc. Brainstorm, Phillips technique 6.6, role playing, and a table including main ideas provided by the patients will be used to assist them in keeping their INR levels in an appropriate range, and the impediments they face will be addressed. All of this will complement the knowledge transmitted by health professionals. A sanitary professional will carry out observations and energizer tasks if necessary.

Group meetings with educational sessions will be organized in a primary health center, and they will take place from Monday to Thursday in the evenings (according to the convenience of the center) with at least 90 min each. It has been estimated that eleven sessions are necessary, including 15 persons each as a maximum in order to complete one session per person. The sessions will all be held in the same classroom and under the management of the expert patient and the observation of the main researcher.

Every patient will be required to attend one group meeting (the intervention group). The control group will perform the usual clinical practice: people will be scheduled to visit with a nurse about once per month, except for cases in which controls are inappropriate who will be scheduled for more frequent visits. Patients in the control group will not attend any of the group sessions. Both groups will be followed with their usual INR controls, carrying out the needed number of measurements under the guidance of the health professionals involved in the appropriate INR control of all patients.

As the final step, once the intervention had been carried out for every indicated patient, INR figures and data will be collected over the next 6 months. The study participants will be able to withdraw their informed consent at any time, and they will be free to leave the study if they do not want to complete the 6 months of INR control after the educational intervention. The main reasons for discontinuing or modifying the interventions assigned to each study participant will be a withdrawal request, a participant’s death, or stopping the use of antivitamin K drugs. Unmasking will be allowed in those cases.

Protocol amendments will be reported to the research ethics committee and to the funding foundation (FIMABIS) and trial sponsor ([name]).

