### Timetable and work program

The study is being carried out over a 28-month period. The assembly of the project took place on 1 day at the Primary Care Center *Ciudad Jardin* practice classroom for all healthcare members involved in the research, along with the expert patient who will execute the intervention. The nurses will explain to the participants about the study approach, and they will collect the consent forms from the participants.

In the first step, at the start of the study, a retrospective data collection of the 6 months prior to the intervention will be completed from all patients who meet the selection requirements and are included in the AOT program. Once the anticoagulated patients have been analyzed and the list of the patients on inappropriate control has been completed, a random sampling will be done in every health center in order to build two groups: *intervention group and control group*.

The intervention group will include the indicated patients. Nurse students will take on the telephone calls to schedule intervention group patients for group meeting attendance. The main researcher and the expert patient will attend every group meeting, but the researcher will act just as an observer. Every participant center will rely on nurses (10 partners) and two resident medical interns (learning Family and Community Medicine) to complete this task. Due to their frequent contacts with anticoagulated patients, the nurses will instruct them about study issues and will collect the signed written consent forms; also, they will be involved in data collecting, INR figures, and patient study variables.

A portfolio with the collected data forms will be distributed to every participant. It will be employed by the patients to collect their data, which will be transcribed to a digital book. This book will be identical for every participant center and it will be used as a basis for the randomization. Two resident medical interns will handle all of the computerized recordings.

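### The order of consent, allocation and session booking is inconsistent, and under one reading entry and retention can differ by arm

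*Protocol article*

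**What the plan says.** All places are in the protocol article.

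- **Inclusion criteria:** written informed consent is a condition of entry. Its timing relative to allocation is not given.
- **Step II:** poorly controlled patients are put in number order ("Once the inappropriate individuals are identified, they will be consecutively placed considering their social security number in every health center"), and the next sentence reads "After that, patients in each strate (PCC) will be randomly distributed in the intervention group or the control group". The same section allows 10% loss and counts as losses people who do not wish to take part and people who miss the scheduled meetings.
- **Description of the intervention, opening paragraph:** patients are telephoned, informed and asked about their interest. Then "At the same time, they will be scheduled for the group meetings", and after that "Signed informed consent forms will be obtained when the patient attends the health center before the group meetings begin". Random distribution within centre is mentioned next. On concealment: "The allocation concealment mechanism consists of organizing patients considering their Andalusian Health Service Number of Clinical Record (AHNCR".
- **Description of the intervention, later:** all patients under study receive an information sheet and "they will sign informed consent forms when they attend to INR control appointments". Controls attend no group session.
- **Timetable and work program:** once the "list of the patients on inappropriate control has been completed, a random sampling will be done in every health center". Telephone calls are then made to schedule intervention-group patients.
- **Statistical analysis:** an intention-to-treat analysis is named, and its population is not described.

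**The concern.** Randomisation protects the comparison only if the decision to enter cannot depend on the arm. Two features of the text put that at risk.

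First, if patients are allocated from the screening list and sign afterwards, intervention patients decide knowing that they are expected at an evening session of at least 90 minutes. Control patients decide about nothing beyond their usual visits. The protocol itself, under risks and limitations, expects poor attendance from lack of interest or motivation. That trait plausibly goes with adherence and INR control.

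Second, a missed meeting counts as a loss, and group meetings exist in one arm only. Even among signed patients, the intervention arm could shed its less motivated members while the control arm keeps its own.

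Both would move the comparison of time in therapeutic range towards the intervention.

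**Working it through.** **1. Can one order satisfy every section?**

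- *Allocation first* (list, allocate, call and book, sign) fits Step II and the timetable. It conflicts with the opening paragraph of the description of the intervention if its sentences are in time order, since signature there comes before random distribution.
- *Consent first* (list, sign, allocate, call and book) fits the inclusion criterion and consent at INR appointments. It conflicts with booking in the first call, before signature.
- *The sentence order of that paragraph* (call and book, sign, allocate) books sessions before anyone has an arm, although controls attend none. Either the arm is known at booking, or future controls are booked too.

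No single order fits all the sections.

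**2. What allocation first could do to the estimate.** The documents give no refusal rates and no prognosis for refusers, so every input here is assumed. Let p be the proportion of an allocated arm that does not enter or is dropped. Let G be the gap in mean TTR between those who stay and those who do not, equal in both arms. The mean among those who stay is the whole-arm mean plus p × G. With no treatment effect, the spurious difference is

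(p_intervention − p_control) × G.

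With G = 10 points:

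| Differential | Spurious difference |
|---|---|
| 5% | 0.05 × 10 = 0.5 points |
| 15% (20% vs 5%) | 0.15 × 10 = 1.5 points |
| 30% | 0.30 × 10 = 3.0 points |

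As an anchor in the protocol's own figures, 10% loss of 312 is 31.2 patients. If all fell in one arm of 156, that would be 31.2/156 = 20% against 0%, or 0.20 × 10 = 2.0 points.

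**3. A harsher illustration, also assumed.** Half the patients are motivated and have outcomes D points better, all of them sign in both arms, 90% of controls sign, and the SD is 25. The mean among signers rises by D × 0.5 / (proportion signing).

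- Intervention consent 70%, D = 10: 5/0.7 − 5/0.9 = 1.6 points, type I error about 8%.
- Intervention consent 50%, D = 15: 7.5/0.5 − 7.5/0.9 = 6.7 points, type I error about 47%.
- Equal consent of 90%: no bias, type I error 5%.

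The second case has a differential of 40%, outside the range in step 2.

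**4. Scale.** The planned difference is 15%, not stated as absolute or relative. If it means 15 TTR points, then 0.5–3 points is 0.5/15 = 3% to 3/15 = 20% of it.

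**5. Concealment.** Concealment means that those who enrol, and the patient, cannot learn the next assignment before entry is final. Sorting a list by record number fixes its order but hides no assignment. Replacing names with numbers after assignment masks the outcome data, which is a separate safeguard.

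**The case against.** The strongest reply is that consent first is what the authors mean. Consent is an inclusion criterion, and Step II recruits according to the criteria before it describes random distribution. The opening paragraph of the description of the intervention mentions signature before distribution. The timetable says that data forms given to participants are transcribed to a digital book that serves as the basis for randomisation, which suits enrolment before allocation. This reading is tenable, so a reader who infers that the protocol plainly randomises before consent goes too far. Yet no sentence says that consent precedes allocation, and two sections describe allocation straight from the list.

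A reader might also infer that an intervention patient who skips the session can never become eligible. The text does not support that: all patients under study may sign at INR appointments, both arms keep those appointments, and non-attenders are invited to the next session. Consent before the group meetings begin can also mean any visit before the sessions start.

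The first call may be separate from the later calls to intervention patients, and no arm is named for it. So it is not established that the arm is known then, although booking a session in that call is hard to explain otherwise.

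On concealment, nothing says that recruiters know the list order, and a fixed external order limits steering of individuals. That stands, but it does not turn sorting into concealment.

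Finally, Step II speaks of scheduled revisions in one place and scheduled meetings in another, so the second may be loose wording for check-ups. Elsewhere in the article, patients' meetings are the group sessions. Nor does the text say that the intention-to-treat analysis is confined to consenting patients. Analysis sets may be detailed in a document not shown.

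**Conclusion.** The concern holds as an inconsistency that leaves a selection risk open. The sections cannot all be followed at once. Under the allocation-first reading, entry and retention can differ by arm in a direction that favours the intervention. The loss rule adds to this if scheduled meetings means the group sessions.

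The size is unknown. About 0.5–3 TTR points follows from assumed differentials of 5–30% and an assumed 10-point gap, and equal consent in both arms gives none. It would be wrong to conclude that the consented arms are no longer the randomised arms, or that the intervention arm is a sample of motivated attenders: the documents show neither. The weakness of the stated concealment mechanism does not depend on which order is intended. The point deserves correction because the remedy is cheap and protects the main comparison.

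**What to change.** State one order and use it in every section:

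1. Complete the screening list in each centre.
2. Obtain written consent from all listed patients at the routine INR visit, as the description of the intervention already allows.
3. Lock the consented list per centre.
4. Have a team member without patient contact randomise within centre. The existing random numbers table is adequate.
5. Only then telephone intervention patients to book sessions.

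Delete the wording that presents ordering by record number as concealment, and remove session booking from the recruitment call. Define the intention-to-treat population as all randomised patients, analysed as allocated. Keep session non-attenders in the analysis through their routine INR records, and do not count them as losses.

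This reorders existing steps and needs no new staff. The cost is time: usual controls are about monthly, so recruitment may run some weeks beyond the stated 1 month.

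The stated study start is 1 September 2018. If allocation has already been done, state the order actually used and report refusals and session non-attendance by arm.
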